#### Motor assessment measures

2.4.1

*2.4.1.1. Aerobic fitness* is assessed using the submaximal testing. In this test a seated recumbent stepper (Model SCIFIT-StepOne) will be used, which provides simultaneous movement of the upper and lower extremities in a continuous stepping motion. During the submaximal exercise test, the participants are asked to move their arms and legs in an alternating pattern at a constant speed of 100 steps per minute and resistance (Watts) will be increased every 3 minutes according to the total body recumbent stepper submaximal exercise test until 85% of age-predicted heart rate max is met or participant can no longer continue due to fatigue (test termination endpoint). During the test, heart rate is monitored using polar heart rate monitors. Ten seconds prior to the end of every stage, heart rate is taken and recorded. Once the test is finished, the participant will continue to step at a comfortable self-selected speed with minimal resistance for 2 minutes or until heart rate returns to near baseline levels.^[27]^ The outcome measure is predicted VO2 max calculated by a formula using the participant age, sex, weight, watts used, and HR.^[27]^

*2.4.1.2. Balance and mobility* are assessed using the following assessment tools:

1.6-minute walk test will be used to assess physical endurance capacity.^[28]^ This test needs a hallway with 2 cones 15 meter apart to be performed. The participant walks between the 2 cones for 6 minutes. Distance is measured by number of laps to be completed.2.The Arabic version of the dynamic gait index will be used to examine gait performance and the likelihood of falling ^[29]^. The dynamic gait index has been translated to several languages including the Arabic language.^[30]^3.The Arabic version of the Berg balance scale will be used to assess static balance.^[31]^ It consists of 14 common functional activities that occur in everyday life.^[32]^4.Timed-Up and go test is a test for assessing balance and walking ability.^[33]^ The participant is instructed to rise from a chair, walks 3 meters at a comfortable and safe pace, turns, walks back to the chair, and sits down. The time between the start of the test until the participant sits back on the chair is recorded and used as the outcome measure.5.The Arabic version of the activities-specific balance confidence scale will be used to detect balance confidence.^[31]^ This scale was found to be both reliable and valid for the assessment of balance in PwMS.^[34,35]^6.Barthel index is a self-reported questionnaire that evaluates the ability of individuals to perform activities of daily living and mobility activities ^[36]^. The BI is considered as a measure of disability that had good reliability and validity ^[36,37]^. The BI has been used with individuals with neurological disorders.^[38]^

2.4.1.3. *Upper extremity motor function (UEMF)* is assessed using the following tests:

1.Grip strength of the participants will be assessed using a hand held dynamometer (Model Jamar hydraulic hand dynamometer).^[39]^ Each participant will be instructed to squeeze the handle with maximum strength first on the dominant hand and then on the non-dominant hand. Three trials on each hand will be performed. The average maximum force exerted from the 3 trials will be used as a primary outcome measure.2.9-hole peg test is a specific test for finger dexterity.^[40]^ The participant is asked take pegs from a container, one by one and put them into holes. Then take the pegs back from the hole, one by one an out them into the container as quickly as possible. The time taken to finish the task will be recorded and used as an outcome measure. The test will be performed first on the dominant hand then on the non-dominant hand.

*2.4.1.4. Fall assessment*: the Arabic version of the falls efficacy scale-international will be used to assess fall.^[41]^ The FES-I is a self-report questionnaire that evaluates fear of falling.

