### Objective

1.1

The purpose of this study is to explore the effect of PTE and WJ-MSCs injection versus PTE alone or WJ-MSCs alone on motor and non-motor symptoms in PwMS. We hypothesize that PwMS who receive the combined treatment of WJ-MSCs and PTE will demonstrate significant improvements on motor and non-motor symptoms compared to those who receive either WJ-MSCs alone or PTE alone.

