### Trial design

1.2

The proposed study utilizes a randomized controlled design to examine the combined effect of a 6-month program on motor and non-motor symptoms in PwMS. This study is single-blinded where the researchers involved in the assessments are blinded to the allocation of the participants to each group. We aim to recruit 60 participants with MS (20 in each group) that will be randomly allocated to 1 of 3 groups using a computer-generated software to either a combined treatment group (PTE + WJ-MSCs), PTE alone control group or WJ-MSCs alone control group after going through a battery of comprehensive assessments (Fig. 1).

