#### Physical therapy exercise) program (control group 2)

2.3.2

The PTE program utilized in this study is partly based on 2 previous published exercise programs that were found to be effective in improving balance and mobility in PwMS.^[7,21]^ Following the physical activity guidelines for adults with MS,^[22]^ we will further add 30 minutes of aerobic exercise to the program. Additionally, we will also follow the guidelines of having a minimum 2 sessions per week of physical activity for PwMS. The PTE program consists of a mixed program including the following types of exercises: balance, resistance, flexibility, and aerobic exercises performed 2 times per week for a total of 6 months. The intensity of the exercise will be progressed throughout the 6 months’ period and consists of 3 stages of progression for the resistance/flexibility and balance programs, and 2 stages of progression for the aerobic exercise program. Participants will be progressed to each stage depending on their tolerance and performance level of the exercises. Each session will take 60 to 80 minutes to finish, and will be supervised by a trained physical therapist (PT). Exercise will be performed in a well-equipped lab space at the CTC at University of Jordan. Following the 6 months supervised program, participants will continue the remaining 6 months of the study period performing a home exercise program (HEP).

The PTE session is divided as the following: pre-exercise vital signs measured using a digital HR/BP monitor, 5-minute warm-up exercises, 10 to 15 minutes of strength and flexibility exercises, 10 to 15 minutes of postural balance exercises, 40 minutes of aerobic exercise on a recumbent stepper machine and a 5-minute cool-down. Vital signs will be taken again post-exercise. Resting periods will be given to each participant before progressing to other forms of exercises and as necessary to decrease levels of fatigue. Participants will be allowed to choose the appropriate days/times to do the sessions upon their convenience but will be encouraged to choose the session every other day to allow a day rest in between. Vital signs, comments, and progress of each session will be documented for every participant using weekly exercise logs.

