### Participant timeline

2.5

Eligible participants will be scheduled for their baseline assessments. They will undergo a comprehensive battery of measures including motor, non-motor, and medical assessments, which will take around 2 to 3 hours to complete. Part of the baseline assessment that include MRI imaging will be performed on another day within a week from the baseline assessment on a time convenient to the participant. Participants will repeat these measures at 3, 6, and 12 months post the baseline assessment (Fig. 1).

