### Statistical analysis

2.9

Statistical Package for the Social Sciences (SPSS) 23.0 (SPSS: Inc., Chicago, IL, USA) will be used to perform all statistical analysis and alpha is set at 0.05. Correlations will be utilized to assess the relationship between the outcome measures of interest. Changes in outcomes at the follow-up scores for within-group and between-group differences will be computed using analysis of variance. Effect sizes of all outcomes will be also computed based on the difference in the change score from base line to follow up.

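### The only outcome labelled primary is grip strength, which the hypothesis never names, while at least 18 measures at three visits share one alpha of 0.05

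*Protocol article*

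**What the plan says.** All references are to the protocol article.

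- **Hypothesis (1.1 Objective).** Participants given the combined treatment "will demonstrate significant improvements on motor and non-motor symptoms compared to those who receive either WJ-MSCs alone or PTE alone". No endpoint or visit is named.
- **Primary label (2.4.1.3, upper extremity motor function).** For grip strength: "The average maximum force exerted from the 3 trials will be used as a primary outcome measure". Both hands are tested, and the text does not say which one is analysed. The same section gives the 9-hole peg time as an outcome measure without calling it primary. For aerobic fitness, "The outcome measure is predicted VO2 max calculated by a formula", again without that word.
- **Visits (2.5 Participant timeline).** "Participants will repeat these measures at 3, 6, and 12 months post the baseline assessment".
- **Analysis (2.9 Statistical analysis).** SPSS "will be used to perform all statistical analysis and alpha is set at 0.05". Then: "Changes in outcomes at the follow-up scores for within-group and between-group differences will be computed using analysis of variance". No outcome or visit is set above another.
- **Size and blinding (1.2 Trial design, 2.7 Blinding).** There are three arms of 20. Only the researchers who carry out the assessments are blinded.

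**The concern.** A trial with many outcomes needs one stated claim to which its error rate applies. Here the text points two ways. It gives the primary label to one measure, and it frames success over two whole symptom domains. The two readings are alternatives:

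- **The label is meant.** The primary test is then on hand grip, with two candidate results (one per hand), and the hypothesis as worded has no primary test.
- **The label is a slip.** Nothing is then ranked, and a significant result on any measure at any visit can be reported as support for the hypothesis.

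Either way a reader of the results could not tell which finding the trial was set up to test. Choosing one after the results are seen cannot restore the 5% level.

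**Working it through.** **The plan's own figures.** The only error rate stated is alpha = 0.05. The sample size is 3 × 20 = 60, given without effect size, SD or power, so there is no calculation to reproduce.

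**Count of measures (2.4.1 and 2.4.2), each instrument once.**
- Motor: predicted VO2 max, 6-minute walk, dynamic gait index, Berg, Timed-Up and go, balance confidence, Barthel, grip, 9-hole peg, FES-I = 10.
- Non-motor: BDI-II, MFIS, PSQI, Epworth, Stroop, symbol digit, pain, SF-36 = 8.
- Total 10 + 8 = 18. This is a minimum: both hands count once, SF-36 counts once, and EDSS, biomarkers, evoked potentials, OCT and MRI (2.4.3) are left out.
- Self-reported: balance confidence, Barthel, FES-I, BDI-II, MFIS, PSQI, Epworth, pain, SF-36 = 9 of 18.

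**Independent between-group tests at 0.05.** The chance of at least one false positive in m tests is 1 − 0.95^m.
- One test per measure: 1 − 0.95^18 = 0.603.
- Each visit tested separately, 18 × 3 = 54 tests: 1 − 0.95^54 = 0.937. Expected false positives are 54 × 0.05 = 2.7.

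**Correlated tests.** The article gives no correlations, so these are assumptions. The check simulated the global null with 20 per arm, 18 measures and 3 visits. It used a one-way F-test for each measure and visit, and t-tests of the combined arm against each comparator at two-sided 0.05. The last two events count only results favouring the combined arm.

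| Event under the null | Independent | 0.3–0.5 between measures, 0.7 between visits | 0.7 and 0.7 |
|---|---|---|---|
| ≥1 significant F-test, one visit (18 tests) | 60% | 42–51% | 28% |
| ≥1 significant F-test, three visits (54 tests) | 94% | 71–80% | 53% |
| Combined arm better than at least one comparator, some measure and visit | 92% | 53–66% | 40% |
| Combined arm better than both on the same measure and visit | 22% | 12–15% | 8% |

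Within-group tests, which 2.9 also plans, are not counted because the hypothesis compares arms.

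**If grip is the primary.** Testing both hands at one visit gives at most 2 × 0.05 = 10%.

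**The case against.** Several points on the other side have force.

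- **A chance finding is not nearly certain.** A reader might infer that from the 94%. That figure needs 54 independent tests and counts differences in any direction between any arms. The hypothesis is directional. With moderate correlation the relevant figures are 53–66% for beating one comparator and 12–15% for beating both, and the wording of 1.1 allows either meaning.
- **Separate testing at each visit is an assumption.** Section 2.9 says only that analysis of variance will be used. One repeated-measures analysis per outcome would also fit, and the 18-test figures are then closer.
- **A multiplicity method may exist elsewhere.** An article can leave it to a full protocol or SAP that is not shown, so its absence is not the finding. What stands is what the article does state: a primary label that does not match the hypothesis.
- **The label may only say which score is taken from the dynamometer.** The indefinite article and the neighbouring descriptions of other tests make that plausible. The sentence would still need correcting.
- **Grip is not irrelevant to the interventions.** It is tempting to argue that the exercise programme targets balance and mobility. But the words "found to be effective in improving balance and mobility in PwMS" in 2.3.2 describe two earlier programmes on which this one is partly based. The trial's own programme also contains resistance exercise, and two of the three arms receive cells. The documents support a mismatch with the hypothesis and no more.
- **Both consequences cannot hold at once.** If grip decides the trial, the many-tests argument does not apply to the primary claim. If it does not, nothing turns on hand grip.

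**Conclusion.** The point holds in this limited form. The count of at least 18 measures, the three visits, the single alpha and the lone primary label can all be read directly from the article. The label either puts the primary test on a measure the hypothesis does not name, or it means nothing and leaves the hypothesis open to support from any measure.

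In the second case the false-positive risk is well above 5% on nearly every reading examined. It runs from 12–15% on the demanding one (combined arm beats both comparators, three visits) to 71–80% for any F-test over three visits. These ranges rest on assumed correlations of 0.3–0.5 between measures and 0.7 between visits, and the three-visit figures also on separate tests at each visit. Stronger correlation lowers them: at 0.7 throughout, 8% for beating both and 53% for any F-test over three visits.

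The defect governs what the trial may claim and should be put right before results are seen.

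**What to change.** 1. Correct the grip-strength sentence in 2.4.1.3 so that it says which score, and which hand, is taken from the test. Keep the word primary only if grip really is the trial's primary outcome; in that case bring 1.1 into line with it.
2. Before unblinding, name one primary outcome at one visit that matches the hypothesis. A performance test scored by the blinded assessor is preferable, because about half of the measures are self-reported by participants who know their treatment. Six-minute walk distance at 6 months is only an example. The choice is the sponsor's, and performance tests still depend on the effort of unblinded participants.
3. State whether the combined arm must beat both single treatments or either one. If both, each comparison can be tested at 0.05. If either, adjust for the two comparisons, for example 0.05/2 = 0.025 each.
4. Apply alpha 0.05 to that claim alone. Put a few key secondary outcomes under Holm, including at least one non-motor measure so that this half of the hypothesis is still tested.
5. Report all other measures and visits as exploratory estimates with 95% confidence intervals.

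The cost is a change of wording, with no new data. The downside is that fewer outcomes can be called significant.

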#### Non-Motor assessment measures:

2.4.2

*2.4.2.1. Depreesion* is assessed using the Arabic version of the Beck depression inventory-II.^[42]^ The Beck depression inventory-II measures how depression is manifested in behavior. It not only identifies varying levels of depression but is also able to indicate changes in intensity of depression over a period of time. Ratings are summed to provide a total score ranging from 0 to 63.^[43]^

*2.4.2.2. Fatigue* is assessed using the Arabic version of the modified fatigue impact scale (A-MFIS). The MFIS is a 21 item self-administered questionnaire that offers multidimensional assessment of the effects of fatigue in terms of physical, cognitive, and psychosocial functioning.^[44]^ The MFIS was translated into the Arabic language and was found valid and reliable tool to assess fatigue in people with MS.^[45]^

*2.4.2.3. Sleep quality* is assessed using the following tests:

1.The Arabic version of Pittsburgh sleep quality index will be used to assess sleep quality.^[46]^ Pittsburgh sleep quality index is a well-validated and reliable measure of global sleep quality which consists of 19 self-rated questions. These 19 questions form 7 component scores, each of which is rated on a scale of 0 to 3 with 0 indicating no sleep difficulty and 3 indicating severe sleep difficulties. The 7 component scores are then summed to form a single global score ranging from of 0 to 21. A global score of 5 or more reflects poor sleep quality for all age groups.^[47]^2.The Arabic version of Epworth sleepiness scale (ESS) will be used to assess the daytime sleepiness.^[48]^ It consists of 8 items where the participant uses a 4-point Likert scale to rate how likely they would be to fall asleep in 8 different scenarios of daily activities.^[49]^

*2.4.2.4. Cognitive assessment* will be examined using the following measures:

1.The Stroop test is a tool performed as a measure of executive functioning that requires participants to inhibit the natural response (reading a word) and replace it with another response (saying a color) ^[50]^. A validated Arabic version will be used in this study.^[51]^2.The symbol digit modalities test, oral form, is a measure of information processing speed that asks participants to quickly say the number that matches a corresponding symbol ^[52]^. The total correct responses in 90 seconds will be used as the outcome measure.^[52]^

*2.4.2.5. Pain* is assessed using the pain rating scale that was translated into the Arabic by the British pain society and recommended for use in populations where pain is a major issue.^[53]^

*2.4.2.6. Quality of life (QOL)* is assessed using the short form SF-36 (SF-36 version-1). The SF36 is a health-related quality of life measure.^[54]^ An Arabic version of the SF-36 has been validated.^[55]^

#### Medical assessment

2.4.3

*2.4.3.1. Clinical disability assessment* is examined using the EDSS. The EDSS is the MS golden standard that assesses the degree of disability.^[56]^ The EDSS is performed by a trained internal medicine specialist under the supervision of the lead neurologist from Jordan University Hospital. It is a scale from 0 (very minimal signs of MS with no disability) to 10 (Death due to MS) with an increment of 0.5. An EDSS change of 0.5 or 1.0 point or more in either direction is considered as a significant change.

##### Biological markers

2.4.3.1

Bio-specimens including blood and cerebrospinal fluid are collected from participants by a trained nurse. Inflammatory markers in the blood are examined using Multiplex ELISA technology. Neural regeneration markers will be measured in the CSF and blood collected. Tests will be performed by CTC biotechnologists. Moreover, the percentage of T, B and NK cells in the blood of participants will be calculated at the CTC flow cytometry lab by a dedicated biotechnologist. Additionally, the IgG levels in the CSF will be measured in a referral CAP accredited lab (MEDLAB).

The difference in concentrations compared to baseline measurements of biomarkers in the blood and CSF of patients in pg/mL enables the evaluation of the inflammatory and neural regeneration/degeneration status in response to interventions. While a change in the percentages of the different immune cells in participant's blood is an indication of immune-modulation outcome.

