### Eligibility criteria

2.2

Interested participants will be checked for the inclusion/exclusion criteria where they will undergo a thorough neurological exam performed by a neurologist to generate the expanded disability status scale (EDSS), and a trained research personnel will perform the mini mental state examination.^[18]^ A screening form is also filled out for every participant that includes demographics, general history of the disease, past, and current medication intake and relevant clinical aspects of the disease. Participants will be selected based on the following eligibility criteria:

Inclusion criteria:

(1)Males and females.(2)Eighteen years and older.(3)Written informed consent prior participation.(4)Independent in ambulation even with the use of an assistive device.(5)All types of MS.(6)EDSS score < 6.5.(7)mini mental state examination score ≥ 24.

Exclusion criteria:

(1)Uncorrected vision loss.(2)History of a nervous system disorder other than MS.(3)Severe physical, neurological, or sensory impairments that would interfere significantly with testing.(4)Developmental history of learning disability or attention-deficit/hyperactivity disorder.(5)Relapse and/or corticosteroid use within 4 weeks of assessment.(6)Acute ischemic cardiovascular event or coronary artery bypass surgery less than 3 months.(7)Uncontrolled blood pressure with medication (blood pressure (BP) > 190/110 mm Hg).

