## Discussion

3

In this study we will investigate the combined effect of stem cell therapy and physical therapy exercises in a wide range of MS symptoms. Moreover, we will compare the effect of a combined therapy to the separate effect of each therapeutic intervention alone. This will help health care professionals dealing with PwMS to have a better understanding of the combined versus separate effects of each therapeutic intervention. The outcomes from this study may help in reducing the cost associated with the life-time care of these individuals worldwide. More importantly, this study may help improving patients’ QOL and reducing their disability. For rehabilitation specialists, neurologists, and regenerative medicine specialists, the outcomes of this trial would clarify the added value of the regenerative interventions with the physical therapy exercise on different symptoms that PwMS suffer from. This will allow them to have a better understanding of this combination to answer PwMS questions that they usually have. Moreover, the combination between biological interventions and having the patients physically active through regular and progressive exercises would emphasize the benefits that the patients may get from both techniques. The expected benefits from both interventions could lead to a medical breakthrough in the treatment of PwMS. This would have positive socio-economic impact, including reducing the treatment cost related to the chronic nature of the disease and getting this active segment of the society back to the work market.

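### Biomarker change from a participant's own baseline is read as a response to treatment, with no comparator arm named and every arm treated

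*Protocol article*

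**What the plan says.** The section headed Biological markers gives the form of the marker results and how they are to be read. For concentrations in blood and CSF, the difference from the baseline measurement "enables the evaluation of the inflammatory and neural regeneration/degeneration status in response to interventions". For T, B and NK cells, "a change in the percentages of the different immune cells in participant's blood is an indication of immune-modulation outcome". No direction, size or comparison arm is attached to either statement.

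Section 1.2 (Trial design) allocates participants to "either a combined treatment group (PTE + WJ-MSCs), PTE alone control group or WJ-MSCs alone control group", and the target is stated as "We aim to recruit 60 participants with MS (20 in each group"). No arm is untreated, sham-treated or on usual care alone. Measures are repeated at 3, 6 and 12 months (section 2.5).

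Section 2.9 (Statistical analysis) sets alpha at 0.05, plans analysis of variance for changes within groups and for differences between groups, and adds effect sizes built on change scores. It does not rank the two kinds of comparison. The hypothesis in section 1.1 is between-group: combined treatment against each treatment given alone.

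**The concern.** A change from baseline within one arm contains the treatment effect, if there is one, plus everything else that moves a marker over 3 to 12 months: the course of the disease, regression to the mean and assay drift. An untreated arm would show those other components. This trial has none, so only the randomised differences between arms remove them.

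The Biological markers text attaches the words about response and immune modulation to the quantity that does not remove them. Section 2.9 leaves this open, because a within-group result has the same standing there as a between-group one. A report could follow the protocol, find a significant change in the WJ-MSCs arm, or even in the PTE-alone arm, which receives no cells, and call it immune modulation. The mechanistic conclusion could then be positive when the cells do nothing.

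**Working it through.** The protocol gives no marker SD, threshold, drift or power figure, so there is nothing of its own to reproduce beyond 3 × 20 = 60. The check has two steps.

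**1. What each comparison identifies.** Let *m* be the mean drift that all randomised arms share in expectation, and let *e* with a subscript be the effect of an arm's treatment on the marker.

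- Within-arm change: *m* + *e*(arm). With no untreated arm, *m* is not estimable.
- Combined minus PTE alone: [*m* + *e*(combined)] − [*m* + *e*(PTE)] = *e*(combined) − *e*(PTE), the effect of adding WJ-MSCs to PTE.
- Combined minus WJ-MSCs alone: *e*(combined) − *e*(WJ-MSCs), the effect of adding PTE to WJ-MSCs.

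Drift cancels in the two between-arm contrasts and stays in the within-arm change.

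**2. Illustration of size.** Inputs from the protocol: n = 20 per arm and alpha 0.05. Assumptions: two-sided test, no treatment effect, normal change scores, and the same drift *d* in every arm, in SDs of the change score. The within-arm test is a one-sample *t* test with 19 degrees of freedom and noncentrality *d*√20. The between-arm test is a one-way analysis of variance on the same change scores (20,000 simulated trials).

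| Assumed drift *d* | *d*√20 | One arm shows a significant change | Between-arm test significant |
|---|---|---|---|
| 0 | 0 | 5.0% | 5.2% |
| 0.2 | 0.89 | 13.6% | 4.8% |
| 0.3 | 1.34 | 24.7% | 5.1% |
| 0.5 | 2.24 | 56.5% | 5.2% |

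If any one of the three arms may be called a responder, the chance for a single marker is 1 − (1 − p)³:

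- *d* = 0: 1 − 0.950³ = 14%
- *d* = 0.2: 1 − 0.864³ = 36%
- *d* = 0.3: 1 − 0.753³ = 57%
- *d* = 0.5: 1 − 0.435³ = 92%

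The between-arm rate does not move with *d*, as step 1 requires; its small departures from 5% are simulation error.

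**The case against.** The marker text stands among the outcomes. It can be read as describing what is measured and in what form, with the comparison left to section 2.9. That section does plan between-group analysis, and section 1.1 states a between-group hypothesis on symptoms, not on mechanism. On this reading the valid contrast already exists, and the marker text is only loosely causal. Much of this stands: the randomised comparison is planned, and common drift does not bias it. It does not settle the point, because section 2.9 also plans within-group tests without calling them descriptive, and the only text on how to read the markers points to change from baseline.

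The drift values are also assumed. That stands too, and the percentages should be quoted only as an illustration.

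A reader might go further in two ways that the documents do not support.

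- **The entry window as the cause.** The protocol excludes "Relapse and/or corticosteroid use within 4 weeks of assessment" and admits "All types of MS", so one might infer that recovery from a recent relapse or steroid course drives the drift. The documents do not say that markers are still settling after 4 weeks, or how many participants would enter soon after the cut-off. The illustration does not fit that cause well either. If 20% of an arm were such participants (an assumption), an arm-wide drift of 0.3 SD would need a shift of 0.3/0.2 = 1.5 SD in each of them, and 0.5 SD would need 0.5/0.2 = 2.5 SD. The point does not need this mechanism.
- **The Discussion as a claim against no treatment.** The Discussion promises a "better understanding of the combined versus separate effects of each therapeutic intervention". This can fairly be read as combined treatment against each single-treatment arm, which the design does identify. It needs no change.

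**Conclusion.** The point holds as a matter of interpretation. The protocol links own-baseline marker change to treatment response and immune modulation, names no comparator, and does not say that the between-group result decides. With three treated arms, a within-arm change cannot carry that conclusion.

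That conclusion follows from the design and needs no figure. Its numerical size cannot be derived from the documents: the 14% to 57% per arm, against about 5% between arms, rests on the assumed common drift of 0.2 to 0.5 SD and on no treatment effect. It should not be inferred that the trial's randomised comparisons are biased or that its main hypothesis is affected. The defect is confined to how the biomarker results may be read, and it is worth correcting because the correction is nearly free.

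**What to change.** In the Biological markers section and in section 2.9, state that:

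- conclusions about markers rest on the randomised difference between arms at follow-up, adjusted for the baseline value of the marker;
- combined versus PTE alone addresses adding WJ-MSCs, and combined versus WJ-MSCs alone addresses adding PTE;
- this applies to each marker, in blood or CSF, that is measured in both arms being compared;
- changes within an arm are reported as descriptive and are not called a response or immune modulation.

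No new arm, visit or specimen is needed. The cost is a weaker mechanistic claim for each single arm and some loss of precision. On unadjusted change scores the standard error is SD × √(2/20) = 0.32 SD for a difference between two arms, against SD × √(1/20) = 0.22 SD for one arm's mean change. Baseline adjustment may recover part of that.
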